## Abstract

Supplemental Digital Content is available in the text

## Introduction

1

Depression is a serious mental health disorder. It is generally characterized by sadness, loss of interest in activities, and decreased energy.^[1]^ Evidence suggests that the onset of major depression predominantly manifests during adolescence. Furthermore, it influences a child's psychological, social, and academic functioning. Due to this, they will be vulnerable to the risk of substance abuse and suicidal behavior.^[2,3]^ In developing countries, depressive disorders represent a key determinant of health-related disability, and they are considered a major source of nonfatal disease in developed countries.^[4,5]^ Globally, it is estimated that almost 350 million people suffer from depression.^[6]^

In Saudi Arabia, a study has shown that the prevalence of depression among male secondary school students in Abha City is 38.2%.^[7]^ Another study done in the same region found depression in 13.9% of female students.^[8]^ A study done in Al-Ahsa found the symptoms of depression in 24.4% of King Faisal University students. Suicidal ideation in the past 4 weeks was reported by 1.1% of students. Major depression was significantly higher among females.^[9]^ Another study found that the prevalence of depression was 22.4% as moderate, 7.3% as severe, and 3.7% as very severe, with depression occurring 1.5 times more often in girls than in boys.^[10]^

Considerable amount of the current literature pays particular attention to the importance of educational intervention for depression literacy.^[11]^ Rahman et al^[12]^ argued that the school programs succeeded in improving awareness of mental health in school children and the community. The school children were receptive to the program, and shared their new understanding with family, friends, and neighbors. An Internet-based intervention study conducted in Australia suggests that brief mental health literacy and destigmatization improves knowledge and may decrease stigma but does not increase help-seeking for young elite athletes.^[13]^ Another study conducted in Sweden suggested that 42.7% of the respondents identified depression. Depression was recognized more often by women than men. Professional help was suggested by a minority of the respondents for managing symptoms of depression.^[14]^ Overall, these studies highlight the need for educational intervention about depression literacy at the school level. As far as we are aware, there is no similar study conducted in Jazan area that deals with depression.

The main objective of this study is to measure the effect of an educational intervention program about depression on depression literacy and stigma among secondary schools in Jazan City, during the academic year of 2016.

## Methods and analysis

2

### Trail design, study area, and target population

2.1

A cluster-randomized trial design will be employed for this study. The study will be conducted in Jazan City, the capital of Jazan region, lies in the south-western part of the Kingdom of Saudi Arabia. There are 13 governmental secondary schools (6 for boys and 7 for girls) in Jazan City. Inclusion criteria involves; students who are enrolled in one of the selected schools; participants in the age group of 10 to 19 years, and students who agreed to participate in the study (consent will be obtained from students, and proxy consent will be obtained from guardians). There were no exclusion criteria for participation in this study.

### Sampling size and design

2.2

The sample size calculation will be conducted to determine the number of participants required. Based on the study's design, an intracluster correlation coefficient (ICC) of 0.02 will be used in sample size calculation based on similar studies,^[15,16]^ and an effect size of 0.5 will be used to detect the medium effect of the intervention based on similar studies by Perry et al^[15]^ and Gulliver et al,^[13]^ which used the same design and assessment tool (the depression literacy questionnaire [D-Lit]). Other parameters for estimating sample size include a 95% confidence interval and an Alpha coefficient of 5%. Accounting for a 10% non-response and/or drop-out rate, the total required sample size will be 360 students, 180 of whom will be recruited for the intervention group and 180 for the control group. The unadjusted sample size calculation will be conducted using the G∗Power program (version 3.1.9.1; Heinrich Heine Universität, Düsseldorf, Germany)^[17]^, then adjusted for the cluster design effect according to the methods outlined in Campbell et al.^[18]^

For sampling procedures in stage one 13 secondary schools in Jazan city will be stratified according to sex (6 schools for boys and 7 schools for girls). In stage two, 1 school from each stratum will be selected at randomly for the control group, and another one from each stratum will be selected at randomly for the intervention group using the closed envelope technique. Finally, in sage three and based on the calculated sample size of 360, random sampling technique will be used to recruit 180 students from the control schools (1 boy's school and 1 girl's school) and 180 students from the intervention schools (1 boy's school and 1 girl's school) (see Figure 1, Supplemental Content which illustrates the sampling procedures).

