##### Lectures

2.3.2.1

There will be 2 lectures of around 30 minutes; 1 lecture will be held each weak. Thirty students will attend each lecture. Therefore, each intervention school (90 students) will be divided into 3 groups (30 students in each); the first lecture will cover recognition, risk factors, and causes of depression. The second lecture will cover depression treatments—including antidepressants and cognitive behavioral therapy—as well as the professional help available and appropriate ways to seek help.

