## Discussion

3

Many studies have concluded that educational intervention centered around the facts about depression and destigmatization improves knowledge and may decrease stigma.^[29]^

Accumulated evidences suggested the importance of educating adolescents about depression, because this is the peak period for the onset of mental disorders, with half of the people who will suffer from a mental disorder having their first episode before 18 years of age.^[30]^ There is some evidence that receiving mental health information at school can result in reductions in stigmatizing attitudes.^[22,31]^ Further research, intervention and activism are needed in the field of mental health in Arab countries to improve the awareness of mental health problems.^[32]^

Despite the need for such program especially in our region, where there is more stigma attitude, no studies or few have been conducted shed the light on this important area of research.

The proposed research will assist in improving mental health literacy on depression following an educational intervention program. Strengths include that the program will be conducted by students’ teachers at their schools, mimicking the natural sitting, which will lead to outcomes that can be generalized. If positive trends result from the present trial, they will support the development of further longitudinal work on a larger scale, for combating the stigma associated with depression, which is urgently needed in this field.

Limitations include the fact that the intervention will be conducted by 2 independent teachers, 1 from each school, but effect of this will be minimized by giving a short training for both teachers so that they would deliver identical programs.

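### With two schools per arm, the 360 students called required give about 80% power for 0.5 SD only if the ICC of 0.02 is taken as known; a test that estimates between-school variance has about 35% (2 df) or 17% (1 df).

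*Protocol article*

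**What the plan says.** Section 2.2 (Sampling size and design) gives the inputs: "an intracluster correlation coefficient (ICC) of 0.02 will be used in sample size calculation", "an effect size of 0.5 will be used to detect the medium effect of the intervention", and "Other parameters for estimating sample size include a 95% confidence interval and an Alpha coefficient of 5" per cent. It allows 10% for non-response or drop-out. An unadjusted G*Power figure is then adjusted for the cluster design effect, and the section concludes that "the total required sample size will be 360 students, 180 of whom will be recruited for the intervention group", with the same number for control. No power is given.

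The same section stratifies schools by sex and draws two per stratum: "1 school from each stratum will be selected at randomly for the control group, and another one from each stratum" for the intervention. Four schools are therefore randomised, out of a larger pool: "There are 13 governmental secondary schools (6 for boys and 7 for girls) in Jazan City" (section 2.1). Section 2.3.2.1 (Lectures) confirms the cluster size: "each intervention school (90 students) will be divided into 3 groups (30 students in each").

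Section 2.4 compares mean scores with t tests, adjusts all tests by the design effect, and uses P<.05 throughout. Neither section 2.2 nor section 2.4 describes any allowance for the number of schools.

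**The concern.** A design effect corrects the variance of the arm difference for clustering. It does not correct for how little four schools reveal about the size of that clustering. Multiplying a G*Power figure by a design effect keeps a critical value near 1.96, which suits many clusters or an ICC known from outside. With two schools per arm, a test that learns the between-school variance from the trial itself has 2 degrees of freedom, or 1 once sex is fitted.

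The description of 360 as the required size is at stake, and so is the meaning of P<.05 in the between-arm comparison. The analysis cannot repair this, because the number of schools is fixed at allocation.

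**Working it through.** **Inputs.** From section 2.2: d = 0.5 (SD = 1), ICC = 0.02, alpha = 0.05 (two-sided assumed, since sidedness is not stated), 10% loss, two schools per arm. From section 2.3.2.1: 90 students per school, so 90 × 0.9 = 81 analysed.

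**1. Reproducing 360.** At 80% power the unadjusted size is 63 per arm. The design effect is 1 + (81 − 1) × 0.02 = 2.60. Then 63 × 2.60 = 163.8, rounded up to 164 per arm; 164/0.9 gives 183, or 366 in total. Inflating by 1.1 instead gives 181 per arm, or 362. Both are within 2% of 360. At 85% power (72 per arm) the total is at least 2 × 188 = 376 before any allowance for loss. About 80% is therefore the power that 360 implies.

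**2. Power with the ICC treated as known.** The effective size is 162/2.60 = 62.3 per arm. The noncentrality is 0.5 × √(62.3/2) = 2.79. Power is 79% with student-level df (322), or 80% by the normal approximation.

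**3. Power with between-school variance estimated from the four schools.** The noncentrality is again 2.79, but the reference distribution changes:

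| Analysis | Critical t | Power | Power by simulation (400,000 runs) |
|---|---|---|---|
| 2 df, sex not fitted | 4.303 | 35.0% | 35.1% |
| 1 df, sex stratum fitted | 12.706 | 17.3% | 17.5% |

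With no loss at all (90 per school), the figures are 36.0% and 17.7%.

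**4. Range over the ICC.** All values other than 0.02 are assumptions. There are 81 analysed per school.

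| True ICC | Power, 2 df | Power, 1 df |
|---|---|---|
| 0.01 | 45% | 21% |
| 0.02 | 35% | 17% |
| 0.03 | 29% | 15% |
| 0.05 | 22% | 13% |

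**5. Ceiling.** With unlimited students per school, the effective size per arm tends to 2/0.02 = 100 and the noncentrality to 0.5 × √(100/2) = 3.54. Power is then 48% on 2 df and 22% on 1 df.

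**6. Type I error of the design-effect test.** The test divides by a standard error built on a design effect of 2.60. If the true design effect is D, its two-sided error is 2 × [1 − Φ(1.96 × √(2.60/D))].
- ICC 0.02: D = 2.60, error 5%.
- ICC 0.03: D = 1 + 80 × 0.03 = 3.40, limit 1.96 × √(2.60/3.40) = 1.71, error about 9%.
- ICC 0.05: D = 1 + 80 × 0.05 = 5.00, limit 1.96 × √(2.60/5.00) = 1.41, error about 16%.

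**7. The same students in 12 schools of 30.** With 27 analysed per school, the design effect is 1 + 26 × 0.02 = 1.52. The effective size is 162/1.52 = 106.6 per arm and the noncentrality 0.5 × √(106.6/2) = 3.65. On 9 df (sex fitted) power is 90%. At ICC 0.05 the design effect is 1 + 26 × 0.05 = 2.30, the noncentrality 2.97 and power 75%.

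**The case against.** The strongest reply is that 35% is not the power of the planned test. Section 2.4 plans t tests adjusted by the design effect. Such a test does not estimate between-school variance from four schools, and its nominal power is about 79%, in line with 360. If the ICC really is 0.02, its type I error is about 5%. This stands. A reader might infer that the trial as planned has 35% power, and the article does not support that unconditional statement. The low figures belong to an analysis that does not borrow the ICC. What remains is that the planned test depends on a borrowed value that four schools cannot verify.

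Other replies carry some weight:
- **The 80% is inferred.** No stated power is contradicted; the claim concerns what 360 implies.
- **Baseline scores could help.** If adjustment for baseline removed r² of the variance at both levels, with r = 0.71 borrowed from the D-Lit retest figure in section 2.3.1 (an assumption), 2-df power would rise to about 56%. That is still short of 80%, and neither the sample size nor the tests in section 2.4 use such an adjustment.
- **The ICC within sex may be below 0.02.** That would raise the 1-df figure, but even an ICC of zero gives only 28%.

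A reader might also infer that the Discussion generalises from two schools without caution when it speaks of teacher delivery "which will lead to outcomes that can be generalized". That goes too far. The sentence rests on delivery by the students' own teachers in their usual setting. The Discussion also lists delivery by two teachers as a limitation and presents positive results as support for larger work.

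**Conclusion.** The point holds in conditional form. The figure of 360 is sufficient for 0.5 SD at about 80% power only if ICC = 0.02 is taken as known. On that footing the planned test is close to nominal at ICC 0.02, but its type I error is about 9% or 16% if the true ICC is 0.03 or 0.05. Without that footing, power is about 35% (2 df) or 17% (1 df, which matches the stratified allocation). Neither reaches 80% at any ICC in the 0.01 to 0.05 range, and recruiting more students in the same four schools does not change that.

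These figures rest on a two-sided alpha, 81 analysed per school, equal school sizes, normally distributed school means and no baseline adjustment. The ICCs other than 0.02 are illustrative.

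**What to change.** **Needed, at the cost of wording only.**
- In section 2.2, state the power for two schools per arm when between-school variance is estimated: about 35% (2 df) or 17% (1 df) at ICC 0.02, with the 2-df range of 45% to 22% for ICC 0.01 to 0.05.
- In section 2.2, stop describing 360 as the size required to detect 0.5 SD.
- In section 2.4, state that P<.05 from the design-effect test is conditional on the assumed ICC.

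**Optional, only if schools are not yet allocated.** Spread the same 360 students over more of the 13 schools and recompute the design effect for the new cluster size. For example, three boys' and three girls' schools per arm with 30 students each would give the power in step 7. One lecture group of 30 in each of six intervention schools keeps the present total of six groups (2 schools × 3).

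This option is not cheap. It needs the consent of eight more school managers and so the agreement of nearly every school in the city. It also needs four more trained teachers, and supervision and equipped classrooms at six intervention schools instead of two. Assessment at baseline, immediately after the programme, and at 3 and 12 months would mean 4 × 12 = 48 school-level rounds instead of 4 × 4 = 16. The article places the study in the 2016 academic year, so the option may already be closed; the restatement is needed either way.

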### Data collection instruments and trail phases

2.3

#### Phase one

2.3.1

Pre-intervention assessment through the D-Lit, the depression stigma scale (DSS), and the self-stigma depression scale (SSDS) will be carried out for the control and intervention groups to establish a baseline information. Participants will be asked to provide basic demographic information (sex, age, grade, school level, residence, and nationality).

The D-Lit assesses mental health literacy specific to depression. The instrument was developed by the National Institution for Mental Health Research in Australia, lead developer Kathy Griffiths. The D-Lit questionnaire's Cronbach alpha is 0.70, and its test–retest reliability is *r* = 0.71.^[13]^ The questionnaire consists of 22 true-or-false items. Respondents can answer each item with 1 of 3 options: “true,” “false,” or “don’t know.” Each correct response receives 1 point. Higher scores indicate higher mental health literacy of depression. D-Lit items are about depression symptoms, management, treatment, and duration, as well as differentiation between depression and other mental illnesses.

The DSS is designed to measure stigmas associated with depression. The scale was developed by the National Institution for Mental Health Research in Australia, lead developer Kathy Griffiths. The DSS has 2 subscales, which measure 2 different types of stigma: personal and perceived. The Personal Stigma Subscale measures stigma in the respondents’ own attitudes towards depression by asking them to indicate how strongly they personally agree with 9 statements about depression. The Perceived Stigma Subscale measures the respondent's perception about the attitudes of others towards depression by asking them to indicate what they think most other people believe about the same 9 statements. Responses to each item are measured on a 5-point scale (ranging from 0, “strongly disagree” to 4, “strongly agree”). Higher scores indicate higher levels of depression stigma. Cronbach alpha values for the total, personal, and perceived depression stigma scales were 0.78, 0.76, and 0.82, respectively.^[19]^

The SSDS is designed to assess the extent to which a person holds stigmatizing attitudes towards themselves in relation to having depression. The scale was developed by the National Institution for Mental Health Research in Australia, lead developer Lisa Barney. The SSDS is a 16-item scale with 4 subscales: shame, self-blame, social inadequacy, and help-seeking inhibition. Responses to the self-stigma items are measured on a 5-point scale (ranging from 1, “strongly agree,” to 5, “strongly disagree”). Higher score indicates greater self-stigma. Cronbach alpha values for the SSDS total, shame subscale, self-blame subscale, help-seeking inhibition subscale, and social inadequacy subscale are 0.87, 0.83, 0.78, 0.79, and 0.79, respectively.^[20]^

#### Phase two: intervention

2.3.2

The intervention program will be held in a school setting and supervised by a team consisting of a psychiatrist, a public health physician, and a social worker. The program will be delivered by a teacher from each school after they have received short training to ensure uniformity of the interventions. The educational material will consist of written material created by a specialized team (a psychiatrist, a public health physician, and a social worker). It will be designed according to educational and contact strategies to increase depression literacy and to reduce stigma toward depression for secondary school students and based on studies of mental illness stigma reduction theory.^[21]^ The video, lectures, and group discussion will be presented in equipped classrooms in each intervention school. The intervention will be given over a period of 2 weeks as follows and the educational strategy will be:

##### Lectures

2.3.2.1

There will be 2 lectures of around 30 minutes; 1 lecture will be held each weak. Thirty students will attend each lecture. Therefore, each intervention school (90 students) will be divided into 3 groups (30 students in each); the first lecture will cover recognition, risk factors, and causes of depression. The second lecture will cover depression treatments—including antidepressants and cognitive behavioral therapy—as well as the professional help available and appropriate ways to seek help.

##### Group discussion

2.3.2.2

Each lecture will be followed by a group discussion concerning common myths about depression. After the lecture, for 5 minutes for each myth presented, the students will be divided into groups of 10 for discussion. Myths will be displayed on the monitor, and students will be asked to talk about their opinions, specifically whether they agree or disagree with the myths. After 5 minutes, the teacher will give them the correction for the displayed myth.

##### Brochures

2.3.2.3

A printed brochure will be structured to include several components, including how to recognize depression, risk factors, and causes, treatments for depression—including antidepressants and cognitive behavioral therapy—the professional help available and appropriate help-seeking behaviors. The brochures will be distributed after the second lecture. Students will then be asked to read these brochures for 10 minutes, and they will be encouraged to ask questions about the material.

##### Posters

2.3.2.4

Four posters with mental-health slogans about depression will be distributed around the school in visible places. Poster themes will include the following: “Get support from your doctor, family, friends, and school,” “An untreated mental disorder can lead to more severe and difficult to treat illness,” “If you are worried, sad, angry, or just don’t feel ok, talk to someone about how you feel. Reach out for help. Don’t be afraid,” and “Getting help shares the burden. Believing in yourself makes your load lighter.”

##### Contact strategies

2.3.2.5

Numerous studies support the role of contact with an individual who has personal experience with mental illness in helping to reduce stigma.^[22,23–25]^ Research suggests that video contact can work as effectively as a live presentation.^[26,27]^ Thus, we will show a video of a young man who has been diagnosed (i.e., not an actor) with depression. The video will present information that is moderately disconfirming of prior stereotypes by balancing presentation of the individual's difficulties resulting from depression with his ability to live a normal life.

#### Phase three

2.3.3

Post-intervention assessment by the D-Lit, DSS, and SSDS questionnaires will be conducted for the control and intervention groups immediately after the intervention and during a follow-up after 3 and 12-months.

### Statistical analysis and data management plan

2.4

The main analysis will include the data collected from all respondents. Differences between socio-demographic variables will be examined using chi-squared analyses. The Statistical Package for the Social Sciences (SPSS) (version 20) will be used to analyze the data. Differences between mean scores of D-Lit, DSS, and SSDS for the intervention and control groups—as well as changes in mean scores over time for each group—will be tested with either a paired *t* test or with Welch *t* test when the variances of the 2 comparison groups are not equal. To examine differences between groups at the baseline, Student *t* test—or the Mann–Whitney *U* test if appropriate—will be performed for pre-intervention D-Lit, DSS, and SSDS scores. All tests will be adjusted for cluster design using the design effect.^[28]^*P*-values <.05 will be used in all analyses.

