### Ethical consideration

2.6

This study protocol was approved by a Faculty of Medicine Research Ethics Committee at Jazan University. Consent will be received from the managers of the selected schools. Before participation, students will be informed that the collected information will be kept anonymous and that participation is absolutely voluntary. The participants will be assured that they could withdraw from the study at any time. Informed consent will be sought from the eligible participants following a full disclosure regarding the study. Proxy consent for the children will be obtained from their guardians and from each child who is eligible to participate in the study before randomization.

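### The main analysis is defined by who answered, so enrolled students without a post-intervention score drop out of that comparison, and the 10% inflation of the sample does not protect against selective loss

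*Protocol article*

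**What the plan says.** Section 2.4 of the protocol article (Statistical analysis and data management plan) fixes the main analysis set: "The main analysis will include the data collected from all respondents". It then names the tests. Mean scores on the three instruments, between groups and over time, "will be tested with either a paired *t* test or with Welch *t* test when the variances of the 2 comparison groups are not equal". It adds that "All tests will be adjusted for cluster design using the design effect".

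Section 2.3.3 (Phase three) places the post-intervention assessments "immediately after the intervention and during a follow-up after 3 and 12-months", for both groups. With the baseline in section 2.3.1, that makes four assessments.

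Loss is foreseen in section 2.2 (Sampling size and design): "Accounting for a 10% non-response and/or drop-out rate, the total required sample size will be 360 students". This is one overall rate, not split by arm or by assessment. Section 2.6 (Ethical consideration) adds the usual right to leave: "The participants will be assured that they could withdraw from the study at any time".

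The article does not say that the main analysis covers all enrolled students in the arm of their allocated school.

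**The concern.** Whether a student answers a post-intervention questionnaire is settled after allocation. A main set defined by response can therefore differ between the arms in ways that allocation did not produce. The t tests do nothing to repair this. A between-group test uses whoever has a score at that assessment, and a paired test uses whoever has both scores. The baseline, 3-month and 12-month comparisons can thus rest on different students, and the planned baseline test need not describe the students compared later.

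At stake is what the estimate means. The objective in the Introduction is the effect of the programme among secondary school students. A respondents-only comparison gives the difference among those who kept answering. If students with low depression literacy are lost more often from one arm, that arm's mean rises without any effect of the programme. The plan's only stated answer to loss is a larger sample, which cannot correct this.

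**Working it through.** **Inputs from the documents.** Effect size 0.5 SD, ICC 0.02, alpha 5%, 10% loss, 180 students per arm (all section 2.2); two schools per arm, hence 90 students per school (sections 2.2 and 2.3.2.1).

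**Assumed, because the documents do not give them.** A two-sided test at 80% power; pre-post correlation 0.6; correlation rho of 0.3 to 0.5 between the tendency to drop out and low baseline score; loss of 10% in control and 20% or 30% in intervention; no true effect; standardised scores.

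**1. The plan's own sample size.** The unadjusted size for 0.5 SD is 63 per arm (normal approximation). With 90 × 0.9 = 81 analysed per school, the design effect is 1 + (81 − 1) × 0.02 = 2.60. Then 63 × 2.60 = 163.8. Multiplying by 1.1 gives 180.2 per arm, or 360 in total; dividing by 0.9 gives 182 per arm, or 364. The 360 is reproduced. The match does not prove that 80% was the power used, since some one-sided settings also come close.

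**2. What the inflation buys.** With m students analysed per school, the effective size per arm is 2m / [1 + (m − 1) × 0.02], and power is Φ(0.5 / √(2/effective size) − 1.96).

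| Loss | Analysed per arm | Design effect | Effective size | Power |
|---|---|---|---|---|
| 0% | 180 | 2.78 | 64.7 | 81.2% |
| 10% | 162 | 2.60 | 62.3 | 79.7% |
| 20% | 144 | 2.42 | 59.5 | 77.9% |
| 30% | 126 | 2.24 | 56.2 | 75.5% |

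Precision barely moves. These figures take the design-effect approach as given and say nothing on whether two schools per arm are enough.

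**3. Selection on baseline score.** If a fraction p is lost through a probit mechanism, the baseline mean of those remaining rises by rho × φ(z_p)/(1 − p). The factor φ(z_p)/(1 − p) is 0.195, 0.350 and 0.497 for p of 10%, 20% and 30%.

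**4. Between-arm difference in post-intervention score.** Bias = 0.6 × rho × (difference in factor).
- 20% against 10%: difference 0.155, bias 0.028 (rho 0.3) to 0.046 (rho 0.5) SD.
- 30% against 10%: difference 0.302, bias 0.054 to 0.091 SD.

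This is 0.03 to 0.09 SD towards the programme, or about 6% to 18% of 0.5 SD. If control lost more, the sign would reverse.

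**5. Paired change within an arm.** Those remaining start higher by rho × factor and end higher by only 0.6 of that, so bias = −0.4 × rho × factor.
- 20% loss: −0.042 to −0.070 SD.
- 30% loss: −0.060 to −0.099 SD.

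The between-arm difference in change is −0.4 × rho × (difference in factor): −0.019 to −0.031 SD for 20% against 10%, and −0.036 to −0.060 SD for 30% against 10%. Both run against the programme.

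**6. A second parameterisation.** Bias = p_int × g_int − p_ctl × g_ctl, where g is the responder-minus-nonresponder mean in SD.
- 10% in both arms, equal g: 0.
- 10% in both arms, g = 0.5 in intervention only: 0.05 SD.
- 20% against 10%, g = 0.5 in both: 0.2 × 0.5 − 0.1 × 0.5 = 0.05 SD.
- 30% against 10%, g = 0.5 in both: 0.10 SD.

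**7. Would using the baseline help?** In a simulation of step 4 with rho 0.5 and no true effect, the baseline-adjusted difference was 0.00 SD in both scenarios. That had to happen, because the simulated loss was related to outcome only through baseline. It shows what the fix can remove, not that it removes every selection.

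**The case against.** The strongest reply is that the set of all respondents is inclusive: it excludes nobody for poor attendance, and section 2.3.3 assesses the two groups, not the attenders. That stands. A reader might infer that students who stop coming to the sessions leave the estimate. No section says so, and a non-attender who completes the questionnaire is a respondent.

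Three further inferences go too far.
- *That the arms will lose students unequally.* Only the intervention arm has sessions to miss, but delivery is in the students' own schools, no section places the post-test inside the last session, and no loss by arm is given. Unequal loss is a possibility to guard against, not a fact.
- *That the bias always favours the programme.* Under the same assumptions it favours the programme in the post-intervention scores and works against it in the paired change. Both comparisons are planned.
- *That the withdrawal sentence is a follow-up rule.* It is consent wording, and section 2.2 separately foresees non-response. Detail on continued assessment and on missing scores may sit in documents not shown, so its absence from the article is no fault.

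It is also fair that the set is not expressly redefined at each assessment; this follows from observed-score tests on repeated questionnaires. And the size is modest: at the planned loss the standard error is √(2/62.3) = 0.18 SD, so even 0.09 SD is about half of one standard error.

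What remains is that section 2.4 does not leave the matter open. It names a set defined by response and tests that use observed scores only.

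**Conclusion.** The point holds in a limited form. Section 2.4 bases the main analysis on students who answered, so an enrolled student without a post-intervention score is absent from that comparison, and the only stated provision for loss protects precision alone.

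Under the assumed scenarios of 20% or 30% against 10% loss, the shift is about 0.03 to 0.09 SD towards the programme in the post-intervention comparison, and about 0.04 to 0.10 SD against it in the intervention arm's paired change. It is zero when loss is equal and equally related to score in both arms. The size rests on the assumed correlations and loss rates, none of which the documents supply. This does not invalidate the trial; it is a cheap and worthwhile improvement to a stated choice.

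**What to change.** In section 2.4, replace the sentence that defines the main analysis with wording such as:

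*The main analysis will include all enrolled students, in the arm of their allocated school, regardless of session attendance. Scores from all assessments will be analysed together, with adjustment for baseline, in a likelihood-based repeated-measures model (or after multiple imputation by arm), and the analysis will account for clustering by school. The comparison of respondents by t test will be a sensitivity analysis.*

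The cost is this wording and a modest amount of extra analysis; no further students or assessments are needed. The downside is the assumption that missingness is explained by observed scores: loss driven by unrecorded causes would still bias the result. With only four schools the model itself will estimate the between-school variance poorly, so the clustering adjustment must be specified with that in mind; this change does not solve that separate problem.
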